#### Blood

Blood will be collected from each subject for plasma silymarin concentration determination at the times indicated in the schedule of events tables. Blood samples will be collected with plasma samples transferred to labeled polypropylene tubes, sealed, and stored immediately at -20°C in an upright position until shipped on dry ice.

#### Urine

Two 10 ml aliquots (20 ml total) of urine from each collection interval will be taken and frozen for determination of silymarin concentrations.

Analysis of silymarin concentrations in plasma and urine will be performed using validated analytical methods. All biological samples will be shipped to and stored at the NIDDK repository and then shipped to the testing laboratory for analysis at the discretion of the SyNCH Investigators

The label for each sample will identify the study number and collection date and time.

### **4.4 Follow-up period**

Within two weeks of completing the 48 week treatment period, liver biopsy will be performed, as previously described, while the patient continues on silymarin. Therefore, patients may receive as many as 50 weeks of treatment. Follow up laboratory studies including ALT, AST and HOMAr will be obtained at the time of the liver biopsy. Also, blood will be collected for future studies.

Subjects will be followed for an additional 12 weeks after end of treatment. They will return for post-treatment visits at follow-up weeks 4 and 12. During these visits, participants will be evaluated for resolution of adverse events and laboratory studies will be drawn to measure efficacy. The following procedures will be performed:

|                                  |                                                                                                                                        |
|----------------------------------|----------------------------------------------------------------------------------------------------------------------------------------|
| Interim Medical History          |                                                                                                                                        |
| Symptom-directed Physical Exam   | Vital signs, weight, and physical exam as needed                                                                                       |
| Adverse Event Assessment         | Each visit                                                                                                                             |
| Concurrent Medication Assessment | Each visit                                                                                                                             |
| CBC/Differential                 | Each visit                                                                                                                             |
| Chemistry                        | Each visit: ALT, AST, AlkPO4, total bilirubin, direct bilirubin, albumin, uric acid, BUN, creatinine, glucose
HOMAr at week 12 only |
| Pregnancy Test                   | Urine, Post-treatment week 4 only                                                                                                      |
| Sample Storage                   | 20ml serum, 20ml whole blood, 10ml plasma, 24ml urine each visit                                                                       |
| Questionnaires                   | Week 4: SF-36, CLDQ, CES-D, ASE                                                                                                        |

**4.5 Unscheduled visits:** Participants who have changes in severity or initiation of new symptoms, or who need to have laboratory tests repeated, will be asked to return to the study site for unscheduled evaluations.

## **5.0 Adherence Measures**

It is recognized that there is a significant pill burden (15 capsules daily) for this study. Therefore, an effort will be made to measure adherence to the medication regimen in order to assist with the efficacy analysis and provide information that will be helpful if a phase III study is planned.

### **Adherence Measures**

#### **Procedures**

##### **Patient Education and Adherence Program**

The adherence program for the study will consist of three central components: (a) informational-exchange, (b) skills development, and (c) social support enlistment. One of the tools utilized in this study will be the Medication Adherence Training Interview (i.e., MATI), a structured interview for medication education and adherence training. The MATI has been empirically tested in behavioral medical research in an HIV population and now has been modified for use in patients with NASH. The MATI will be reviewed by study coordinators and used as guidelines for on-going education and addressing medication adherence.

##### **Baseline (day 0)**

During this visit the study coordinator will also engage the participant in goal setting. Participants will be asked by the coordinator to set short-term goals (e.g., achieving a near-perfect adherence rate for the next 30 days) that may be important to the efficacy and safety of silymarin therapy. Participants will also be asked to create self-incentives for attaining the stated goals. The rationale is that individuals achieve greater self-directed change if they reward their successful efforts than if they provide no incentives for themselves.

Participants will be given a diary and asked to record the time of day they ingest each dose of study medication. The coordinator will assist the participant with planning a dosing schedule and integrating the medication times into lifestyle patterns. Participants will be encouraged to keep the portable diaries with them at all times or wherever they store their medications in their home or office. Participants will also be asked to track the number of alcoholic beverages consumed on a daily basis. Participants will be encouraged to create a habit of completing the diary on a daily basis, preferably at the time of ingestion.

##### **Study Visits**

At subsequent study visits, participants will be asked about tolerance to medications and adherence will be stressed. The participant diary will be reviewed thoroughly and used as a tool to facilitate a discussion about adherence. Coordinators will apply strategies outlined in the original MATI to reinforce adherent behavior, and help participants problem-solve areas that need improvement. The tone of the discussion will be supportive and non-judgmental, while assisting the participant in identifying strategies to improve medication adherence. Coordinators will also review daily alcohol consumption and make recommendations when indicated.

##### **Medication Adherence Outcomes**

**Primary:** Cup counts. Patients will be asked to return all full cups to the coordinators. Missed doses (# of full cups returned) will be counted at each study visit.

**Secondary:** Patient self-report of missed doses in diaries. Patients will record the time of day for each dose ingestion in diaries. Study coordinators will record the number of self-reported missed doses on a monthly basis. In addition, silymarin levels measured at the specified visits will be used to identify non-adherent patients.

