## 2.3 Endpoints

**Efficacy:** The primary outcome variable (endpoint) for efficacy is improvement by at least 2 points in histology (NAS).

**Safety:** The primary outcome variable for safety is the occurrence of a dose-limiting toxicity during the 48-50 week treatment period. Adverse events (AE) will be categorized by severity.

**Adherence:** Will be measured using a summary of missed dose information obtained from patient diaries and dose counts and will be analyzed as both an outcome and as an explanatory variable in exploratory analyses of pharmacokinetic exposure and response.

**Biomarkers:** The following relationships will be explored: dose and change in biomarkers, changes in biomarkers and treatment success, changes in biomarkers and toxicity.

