### 6.2 Efficacy Analysis

Tabular and graphical descriptive statistical methods will be used to characterize the study group at baseline in terms of demographic and clinical measures. For each arm of the study, the proportion of participants whose NAS is reduced by at least 2 points ( $\pi$ ) will be estimated

along with corresponding 95% confidence intervals. Point and interval estimates of the distributions of NAS, ALT, fibrosis score, HOMAr, and at baseline will also be tabulated.

The primary null hypothesis, that the proportion of participants whose NAS is reduced by at least 2 points ( $H_{01}: \pi_0 = \pi_1 = \pi_2$ ) will be tested against the general alternative hypothesis,  $H_{a1}$  that response differs in at least one treatment arm via a chi-square test for association with  $\alpha = 0.05$ . If  $H_{01}$  is rejected, then pairwise comparisons of the arms will be examined using a sequentially rejective test procedure (Holm, 1979). Computation of these results for the ITT analysis will comprise the main results of this study.

A per protocol analysis will also be performed. Participants will be included in this analysis if they took at least 80% of the medication.

The null hypotheses of no difference among treatment arms will be tested for the secondary outcomes. For dichotomous outcomes (secondary outcomes 2 and 3 above), the methods described for testing the primary hypothesis will be used. Change in HOMAr will be compared among the groups using either parametric or non-parametric analysis of variance, as appropriate. The null hypothesis of no treatment differences among the three groups for continuous outcomes will be tested using analysis of variance. Post-hoc tests to identify pairwise differences should the null hypothesis be rejected will control for multiple comparisons.

To maximize statistical power, there will not be an adjustment for the multiple outcomes since the results will be used to guide the design of a proposed phase III study.

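### The primary adherence measure counts only full cups returned, so part-taken and unreturned cups score as taken; it can only overstate intake, and the 80% per-protocol rule does not say whether it uses this measure

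*Protocol*

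**What the plan says.** Section 3.4 gives every participant five capsules per dose, three times a day, for 48 to 50 weeks. Section 5.0 acknowledges the load: "It is recognized that there is a significant pill burden (15 capsules daily) for this study".

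Under Medication Adherence Outcomes in section 5.0, the primary measure is a cup count. The return instruction is "Patients will be asked to return all full cups to the coordinators", and the scoring rule is "Missed doses (# of full cups returned) will be counted at each study visit". The secondary measures are diary self-report ("Study coordinators will record the number of self-reported missed doses on a monthly basis") and blood levels ("silymarin levels measured at the specified visits will be used to identify non-adherent patients").

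Section 2.3 describes the adherence endpoint as a combination: "Will be measured using a summary of missed dose information obtained from patient diaries and dose counts". It adds that adherence "will be analyzed as both an outcome and as an explanatory variable in exploratory analyses of pharmacokinetic exposure and response". Compliance Monitoring, within section 4.3, also relies on dose counts plus diary review.

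Section 6.2 makes the intention-to-treat analysis the main result and adds a per-protocol analysis: "Participants will be included in this analysis if they took at least 80% of the medication". It does not say which adherence measure decides this, or whether the percentage is of doses or of capsules.

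**The concern.** A dose is five capsules, but the primary measure has only two states for a cup: returned full (missed) or anything else (taken). A cup with capsules left in it, a cup thrown away and a cup left at home all fall in the second state. No sentence in the protocol asks for part-used cups or for a count of leftover capsules.

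The protocol measures adherence to help interpret efficacy and to inform a phase III study. Overstated intake would bear on three things: the reported adherence at this pill burden, the exploratory use of adherence to explain response, and possibly membership of the per-protocol set. For part-taken cups it would also blur the dose contrast. Three of five capsules in the 700 mg arm is 3 × 140 = 420 mg, which is the other arm's dose. In the 420 mg arm (three active and two placebo capsules), three of five capsules is between 140 and 420 mg, depending on which are taken.

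A statistical analysis plan cannot repair this afterwards. What comes back to the site and what is counted there is fixed by the protocol, and leftover capsules that were never counted cannot be recovered.

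**Working it through.** **Inputs.** Five capsules per dose and three doses a day (sections 3.4 and 5.0); 48 to 50 weeks (section 3.4); the 80% threshold (section 6.2); missed doses equal full cups returned (section 5.0). The protocol states no adherence percentage, so there is no figure to reproduce.

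Two assumptions are needed. First, one cup holds one five-capsule dose, which section 5.0 implies but does not state. Second, the score is 1 − (full cups returned ÷ doses prescribed), because the protocol gives no formula.

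**Doses at stake.**
- 48 weeks: 3 × 7 × 48 = 1008 doses (5040 capsules). Since 0.20 × 1008 = 201.6, up to 201 missed doses still meet 80%.
- 50 weeks: 3 × 7 × 50 = 1050 doses (5250 capsules). Up to 210 missed doses still meet 80%.

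**Part-taken cups.** Someone who takes 3 of 5 capsules from every cup has an intake of 3/5 = 60%, returns no full cup and scores 100%. If a share *f* of cups is taken this way and the rest in full, true intake is 1 − 0.4*f*. That is below 80% once *f* exceeds 0.5, while the score stays at 100%.

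**Whole doses missed, cups not all returned.** Let *t* be the true share of doses taken and *r* the share of missed cups that come back full. The score is 1 − *r*(1 − *t*), and it reaches 80% when *r* ≤ 0.20 ÷ (1 − *t*).

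| True share taken | Largest share of missed cups returned that still scores 80% | Score if half are returned | Score if none are returned |
|---|---|---|---|
| 75% | 80% | 87.5% | 100% |
| 70% | 67% | 85% | 100% |
| 60% | 50% | 80% | 100% |
| 50% | 40% | 75% | 100% |

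If every missed cup is returned and none is part-taken, *r* = 1 and the score equals the truth. Otherwise it lies above the truth.

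**Prescribed interruption.** A one-week hold is 21 cups, and 21 ÷ 1008 = 2.1%. Those doses were not taken, so counting them as missed does not misstate intake. It does lower adherence relative to what was prescribed, so the denominator needs a rule.

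**Whether the other measures fill the gap.**
- *Diary.* Participants note the time of each dose, and coordinators record self-reported missed doses. Both work in whole doses, and no capsule count is described. Combining diary and cup count, as section 2.3 does, can reveal whole missed doses but not part-taken cups.
- *Silymarin levels.* These cannot show non-adherence on placebo. In the active arms, section 1.0 gives a half-life of about 6 hours in healthy volunteers, so a level reflects recent doses only. The week 2 draw described in section 4.3 follows a witnessed dose, and Dose Selection reports high variability in total concentrations.

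**The case against.** The strongest reply is that the cup count does not stand alone. The endpoint in section 2.3 combines diaries with dose counts, the diary is reviewed at visits, and levels are drawn in order to find non-adherent participants. A reader might infer that someone who stops for the last 16 weeks (336 of 1008 cups, 33%) and returns nothing would pass unnoticed. On the cup count alone that person does score 100%. But they would face telephone calls at weeks 36 and 44 and visits at weeks 40 and 48. They would also need a diary with invented dose times and, in an active arm, would have levels drawn at weeks 40 and 48. This part of the reply stands: whole missed doses may well be caught.

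A reader might also infer that non-adherent participants will enter the per-protocol set. The protocol does not support that as a fact. Section 6.2 ties the 80% rule to no measure, and a statistical analysis plan, which was not available for this point, may name one. Nor does anything in the protocol show that part-taking cups is the usual form of non-adherence. The stated pill burden makes it foreseeable, no more.

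What the reply does not answer is the part-taken cup. It is invisible to the cup count and to a diary of whole doses, and levels cannot show it on placebo.

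**Conclusion.** The concern holds as a defect in a stated rule. The primary adherence outcome scores part-taken and unreturned cups as taken, so its error in intake runs only towards overstatement. This assumes that one cup is one dose and that the full cups returned belong to doses that fell due. A participant at 60% intake can score anywhere up to 100%, but the average error in this trial cannot be computed from the protocol.

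The effect on the per-protocol set is conditional: participants below 80% can enter it if the primary measure is the one used.

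The point is minor. A reader might infer that the main efficacy conclusion is at risk, but it is not: the intention-to-treat analysis does not use adherence. The consequence is confined to the reported adherence, the per-protocol analysis and the exploratory analyses that use adherence to explain response.

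**What to change.** In section 5.0 (Medication Adherence Outcomes):
- Ask participants to return all cups: full, part-used and empty.
- Count the capsules remaining at each visit.
- Define adherence as capsules taken (dispensed minus returned) divided by capsules prescribed.
- Check cups not brought back against the diary, report them separately, and show adherence with them counted as taken and as not taken.
- State how prescribed interruptions enter the denominator (about 2% for a one-week hold).

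In section 6.2, name this capsule-based figure as the measure for the 80% rule in all three arms.

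Treating unreturned cups as not taken, without changing the return instruction, would not work. Only full cups are now requested, so every properly taken dose also leaves an unreturned cup, and the self-reported diary would then decide almost every dose.

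The cost is new return instructions and case report form wording, participants bringing back used cups, a few more minutes per visit, and slightly lower reported adherence. The change has to be made while supplies are still being returned, because the counts cannot be rebuilt later.

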## 6.0 Statistical methods

**Randomization:** For the proposed multi-center parallel-arms experimental design with a total of  $N = 120$  patients (30 per Clinical Center), adaptive allocation will be used to minimize the imbalance among treatment arms (overall and within strata). Adaptive allocation will occur by a web-based system, with a manual backup system, devised by the DCC. Participants will be allocated to treatment arm within strata defined by site and diabetes status (yes, no). Adaptive allocation will be performed via a web-based system located in a private and secure area of the server being used for the study. The web-based system will query the user for the information required to identify the stratum and other information to enable checks that the correct patient was assigned (e.g., patient ID, sex) and return the next treatment assignment in that stratum to the user.

### Descriptive Analyses

Tabular and graphical descriptive statistical methods will be used to characterize the study sample at baseline in terms of demographic profile severity of disease and clinical measures. These results will be presented for each arm of the study. The numbers of subjects who drop out of the study or have incomplete data will be described. Descriptive statistical methods will also be used to summarize available measures of compliance recorded during the study by dose level.

### 6.1 Analysis of Safety

All adverse events will be tabulated and summarized by descriptive methods for each arm. Estimates of the toxicity rate for each dose level of silymarin ( $\theta_{420}$ ,  $\theta_{700}$ ) and for placebo ( $\theta_o$ ) will be tabulated along with their 95% confidence intervals.

In safety analyses, the toxicity rates of the three arms of the study will be compared. A test of the null hypothesis  $H_{o1}: \theta_o = \theta_{420} = \theta_{700}$  is not anticipated to be adequately powered due to an anticipated low toxicity rate and findings from the Phase I study, so it is not a primary hypothesis of this phase II study. An idea of the statistical power afforded by the study to the test  $H_{o1}$  can be obtained by considering the simplified scenario in which stopping rules for toxicity are not used, and a chi-square test is used to test  $H_{o1}$ . In the absence of silymarin, the background rate ( $\theta_o$ ) during the treatment period may be as high as 0.05 ( $\theta_o = 0.05$ ). The maximum tolerated rate is  $\theta_{max} = 0.10$ . If both of the toxicity rates for silymarin are 0.10, then there is only a 12% chance that data will be collected which yields rejection of  $H_{o1}$  at  $\alpha = 0.05$ .

### 6.2 Efficacy Analysis

Tabular and graphical descriptive statistical methods will be used to characterize the study group at baseline in terms of demographic and clinical measures. For each arm of the study, the proportion of participants whose NAS is reduced by at least 2 points ( $\pi$ ) will be estimated

along with corresponding 95% confidence intervals. Point and interval estimates of the distributions of NAS, ALT, fibrosis score, HOMAr, and at baseline will also be tabulated.

The primary null hypothesis, that the proportion of participants whose NAS is reduced by at least 2 points ( $H_{01}: \pi_0 = \pi_1 = \pi_2$ ) will be tested against the general alternative hypothesis,  $H_{a1}$  that response differs in at least one treatment arm via a chi-square test for association with  $\alpha = 0.05$ . If  $H_{01}$  is rejected, then pairwise comparisons of the arms will be examined using a sequentially rejective test procedure (Holm, 1979). Computation of these results for the ITT analysis will comprise the main results of this study.

A per protocol analysis will also be performed. Participants will be included in this analysis if they took at least 80% of the medication.

The null hypotheses of no difference among treatment arms will be tested for the secondary outcomes. For dichotomous outcomes (secondary outcomes 2 and 3 above), the methods described for testing the primary hypothesis will be used. Change in HOMAr will be compared among the groups using either parametric or non-parametric analysis of variance, as appropriate. The null hypothesis of no treatment differences among the three groups for continuous outcomes will be tested using analysis of variance. Post-hoc tests to identify pairwise differences should the null hypothesis be rejected will control for multiple comparisons.

To maximize statistical power, there will not be an adjustment for the multiple outcomes since the results will be used to guide the design of a proposed phase III study.

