## 3.0 Study Design

### 3.1 Study summary

This will be a phase II, multicenter, randomized, double-masked, placebo-controlled study to assess the safety and efficacy of a standardized silymarin preparation (Legalon®) for treating patients with NASH, as defined by a NAS score of at least 4 on a baseline biopsy. Participating centers and Principal Investigators in the study are shown in Table 1. A total of 120 subjects will be enrolled at the 4 clinical centers. All subjects will be at least 18 years old, have serum AST or ALT  $>$  40 IU/L and demonstrated fatty liver. After careful evaluation, all eligible subjects will be entered into a 28-day lead-in phase in which they will undergo counseling with respect to diet, exercise, and alcohol consumption. Participants successfully completing the lead-in phase will be randomized to treatment with one of two dosages of Legalon® or a placebo. Legalon® will be administered orally thrice daily for 48-50 weeks. Subjects will be evaluated regularly for adverse events and for monitoring efficacy through blood sampling. After completing therapy, subjects will be monitored for an additional 12 weeks to measure any sustained effects of study medication and to continue to monitor for resolution of any adverse events.

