## **4.2 Baseline/Randomization Procedures**

### *Liver biopsy*

Percutaneous liver biopsy will be performed within 28 days of randomization, during the 28-day period following completion of the lead in phase. The liver biopsy will be performed according to each sites' standard procedures; however, an adequate specimen of at least 1.5 cm in length is recommended. The biopsy core will be processed for histological analysis. The pathologist at each clinical site, or at the central pathology site as described below, will score the liver biopsy according to a grading scheme as described by Brunt et. al. and Promrat et.al., and as modified by the Nonalcoholic Steatohepatitis Clinical Research Network (NSCRN) recommendation. In the NSCRN grading scheme, five features were independently associated with the diagnosis of NASH: steatosis, ballooning, lobular inflammation, fibrosis, and absence of lipogranulomas. A NAS score of at least 4 detected by the local or central pathologist, as determined by each investigator, will be required for entry (Appendix 7).

Four slides from each patient's liver biopsy will be sent to a central pathology site at the Beth Israel Deaconess Medical Center, Boston, MA. The central pathology site will stain the slides (hematoxylin/eosin, trichrome) and the study pathologist will evaluate each biopsy at the end of the study without knowing which slides belong to which patients and assign a NAS. Pre- and post-treatment biopsy NAS will be determined for the primary efficacy analysis. Patients who meet all inclusion and no exclusion criteria at the end of the lead-in period and have liver biopsy findings consistent with NASH (NAS  $\geq$  4) will be randomized. A baseline (randomization) visit will take place within 28 days of successful completion of the lead-in period and following the liver biopsy. During this 28-day period, the inclusion and exclusion criteria will be verified. In addition, the following procedures will take place.

- A history and physical examination will be conducted
- Baseline laboratory studies including liver tests, complete blood count, serum electrolytes, BUN and creatinine, fasting glucose and insulin, and serum silymarin will be obtained
- Fasting serum and urine will be collected for storage and biomarker studies (oxidative stress, apoptosis, and fibrosis)
- Urinalysis
- HOMAr, determined by the formula:

$$\frac{\text{Glucose mg/dL} \times 0.05551 \times \text{Insulin mcUI/mL}}{22.5}$$

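### The primary chi-square test ignores the site and diabetes strata used for allocation; it is valid, but conservative if those strata predict response, and stratifying it costs almost nothing

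*Protocol*

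**What the plan says.** Protocol section 6.0 (Randomization) states: "Participants will be allocated to treatment arm within strata defined by site and diabetes status (yes, no"). Four centers by two diabetes categories give eight cells, and the stated aim is balance both overall and within them.

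Section 6.2 tests the primary null hypothesis "via a chi-square test for association" at a level of 0.05, against the general alternative that the arms do not all respond alike. If it is rejected, "pairwise comparisons of the arms will be examined using a sequentially rejective test procedure". The ITT result of this procedure is called the main result, and the same methods carry over to the dichotomous secondary outcomes. No stratified test and no covariate is named anywhere in section 6.

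Under Liver biopsy, in the section on baseline and randomization procedures, the protocol adds: "Pre- and post-treatment biopsy NAS will be determined for the primary efficacy analysis". A baseline NAS is therefore available to the analysis.

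Section 6.3 assumes response rates of 15%, 40% and 55% with 40 participants per arm, and states 83% power.

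**The concern.** An analysis usually carries the factors on which allocation was balanced. Balance removes the between-stratum part of the variation from the comparison of arms, but the crude chi-square still counts it in its denominator. If the strata predict response, the statistic is too small on average, so the test rejects less often than its nominal level and loses power.

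The protocol's own reasoning makes this worth raising. Its rationale for the subject population stresses control of confounding factors and cites the link between diabetes and NASH. Section 6.2 declines a multiplicity adjustment in order to maximize power. The choice is not left to a later document, because section 6.2 itself names the test.

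Baseline NAS is a related but separate matter. A fall of at least 2 points plausibly depends on the starting score, and that score is not used.

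**Working it through.** **1. The plan's own power figure.** For the planned 2-df test, lambda = n × Σ(p_i − p̄)² / [p̄(1 − p̄)].
- n = 40 and p̄ = (0.15 + 0.40 + 0.55)/3 = 0.3667.
- Σ(p_i − p̄)² = 0.04694 + 0.00111 + 0.03361 = 0.08167.
- lambda = 40 × 0.08167 / (0.3667 × 0.6333) = 14.07.
- Power is 92.9%, or 95.3% by exact enumeration.

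The stated 83% is not reproduced by the planned test. A two-group comparison of 15% with 47.5%, 40 per group, at two-sided 0.025 gives 83.0%. That mismatch is a separate matter. What counts here is that omnibus power at the design rates leaves little to gain.

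**2. Why ignoring balanced strata is conservative.** Let r be the mean within-stratum variance of response divided by the total variance p̄(1 − p̄). With exact balance under the null, the crude statistic behaves approximately as r times a 2-df chi-square. Because P(chi-square with 2 df > x) = exp(−x/2), the size is about 0.05^(1/r):
- r = 1.00 (strata not prognostic): 5.0%
- r = 0.95: 0.05^1.053 = 4.3%
- r = 0.90: 0.05^1.111 = 3.6%
- r = 0.85: 0.05^1.176 = 2.9%

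So the strata must explain several percent of the response variance before the effect shows.

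**3. Simulated size and power of the crude test.** The setting was 120 patients, 30 per site, blocked allocation within site × diabetes, and 8,000 trials per scenario. The documents give none of the following, so they are assumptions: 35% diabetes; baseline NAS 4 to 8 with probabilities 0.30/0.30/0.22/0.13/0.05; log-odds effects for site (standard deviation), diabetes, and NAS per point of 0.3/0.3/0.25 (mild), 0.5/0.5/0.5 (moderate) and 1/1/0.8 (strong).

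| Prognostic strength | Crude size | Power at 15/40/55% | Power at 15/30/40% |
|---|---|---|---|
| None | 5.0–5.3% | 95.3% | 62.0% |
| Mild | 4.3–4.8% | 95.2% | 62.0% |
| Moderate | 4.2–4.7% | 95.8% | 62.7% |
| Strong | 2.9–3.4% | 96.4% | 62.0% |

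The rates 15/30/40% are not in the protocol. They represent a smaller effect than planned.

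**4. What a CMH test stratified by site and diabetes changes.** In a second layout, each of the eight cells held 5 patients per arm. Its log-odds effects for diabetes, site and NAS were 0.7, ±0.5, 0.5 (moderate) and 1.0, ±0.7, 0.8 (strong).
- At 15/40/55%: 95.2 to 95.7% (moderate) and 95.5 to 96.6% (strong).
- At 15/30/40%: 62.0 to 63.5% and 61.1 to 64.5%. Across layouts and assumptions the gain ran from about 0 to 7 points, with 2 to 5 a fair summary for moderate to strong effects.
- With no prognostic effect, CMH costs under 1 point.

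**5. Baseline NAS taken separately.** With a NAS effect alone (0.5 per point), crude size was 4.6–5.3%, so the test is not conservative on that account. At 15/30/40% under the step 3 assumptions, adding NAS to a logistic score test that already held site and diabetes moved power from 67.2 to 70.2% (moderate) and from 71.6 to 78.1% (strong). These logistic score tests ran at a size of about 5.3–6.2%. Even with nothing prognostic they appeared to gain 1 to 2 points, which is not a real gain.

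**The case against.** The strongest reply is that the planned test is simple, prespecified and valid. Ignoring balanced strata creates no false positives and does not bias the compared proportions. In an exploratory phase II trial that is defensible, and supportive adjusted analyses often sit in a statistical analysis plan, which is not at hand. At the protocol's own rates the proposed test gains about a point at most. Nothing in the protocol says how strongly site or diabetes predicts a NAS response, and section 6.0 promises only to minimize imbalance, so the exact balance used in some of the simulations is optimistic. All of this stands, and it sets the size of the point.

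A reader might infer more than the documents support:
- **That the test runs below 5% as a matter of course.** It does so only if the strata are prognostic.
- **That chance imbalance in baseline NAS distorts the result.** It is random variation already covered by the test's error rate, and NAS is not an allocation factor.
- **That stratifying would bring the larger gains seen with NAS adjustment.** Those come from a slightly liberal score test with an extra covariate, not from CMH on site and diabetes.
- **That stratifying would rescue the 420 mg comparison.** Through omnibus plus Holm, 420 mg against placebo has only about 63% power at the design rates, but no pairwise gain from stratifying was computed.

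What survives is that section 6.2 itself fixes a test that does not match the allocation in section 6.0, and that matching them is nearly free.

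**Conclusion.** The point holds as a modest, conditional efficiency matter. The crude chi-square controls type I error. If site and diabetes predict response, its size falls to about 3 to 4.5% under the assumed moderate to strong effects; otherwise it stays near 5%. The power recovered by stratifying is about 0 to 1 point at 15/40/55% and about 2 to 5 points at 15/30/40%. All of these figures rest on assumed prognostic effects, diabetes prevalence and NAS distribution. The direction is secure; the magnitude is not. Omitting baseline NAS is a further, separate loss of efficiency with no effect on validity.

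**What to change.** In Protocol section 6.2:
1. Make the primary omnibus test a Cochran-Mantel-Haenszel general-association test stratified by site and diabetes status as used for allocation.
2. Stratify the Holm pairwise tests in the same way. Say whether the dichotomous secondary outcomes, which inherit the primary methods, follow suit.
3. Keep the crude chi-square as a sensitivity analysis.
4. Add a supportive logistic model with arm, site, diabetes status and centrally read baseline NAS. Use it for estimation rather than as the primary test, given its slightly liberal size at 120 patients.

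The cost is wording only, with no new data. The eight cells average 120/8 = 15 patients, and the power given up if the strata are not prognostic is under 1 point. The change should be made before unmasking, because covariates chosen afterwards would be open to challenge.
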